**Primary Endpoints**

**This is pilot study**

**The primary endpoint is the testing of the rigour of the study methods and design.** To determine the power needed for a large scale study for the investigation of subjects with self diagnosed adverse reactions to aspartame.

To study the acute effects of aspartame on psychological symptoms, biochemistry and metabonomics.

**Secondary Endpoints**

To validate that the product used for the trial is optimal and fit for purpose

To ascertain the optimal design for the main study.

To validate the questionnaire tools for the identification of symptoms of adverse events in individuals reporting self diagnosed adverse reactions.

To validate the biochemical assays in individuals reporting self diagnosed adverse reactions.

**Subject selection**

This study has 2 groups of subjects, those who report having symptoms when consuming aspartame and those who consume aspartame with no ill effects.

The study will recruit 50 subjects in each group.

The responders will be approached by the lobby and interest groups who have accumulated a list of individuals who have an interest in aspartame and report side effects when consuming it. Information will be provided to these groups and a letter with a summary information sheet will be provided to these group to distribute amongst their members. Then the individuals who are interested in taking part in the study will contact the research department to arrange an appointment.

The healthy volunteers will be recruited via a poster and they will be encouraged to contact the research department for study information. The poster will be displayed in primary care centres, university buildings and within the hospital trust. Following subjects contacting the research centre, information will be sent out, following the receipt of the information subjects will be allowed to read the information and asked if interested in further participation in the study, if so a screening appointment will be arranged.

Number of centres involved:

One NHS site: Hull and East Yorkshire Hospitals NHS Trust

One Academic site: University of Hull

Over 1000 side effect reports have been collated by interest groups in the UK, therefore about 100 are likely to be from the Yorkshire region, therefore before requiring subjects to travel excessive distances about 50% of the local individuals who respond to aspartame will need to be recruited. The recruitment of healthy volunteers is not foreseen to be a problem as the organisations who will be displaying the posters employ over 10,000 people and have even greater numbers accessing their buildings every month.

**Inclusion criteria:**

***Healthy volunteers***

No known allergies

No concomitant medical condition

No medication

***Aspartame reactors***

Reported effect of aspartame on ingestion

No allergies to other food substances

**Exclusion criteria:**

***Healthy volunteers***

Allergies to food or medication

A concomitant medical condition

Prescription medication

Refusal for GP to be informed

***Aspartame reactors***

Allergies to food or medication

A concomitant medical condition

Prescription medication

Refusal for GP to be informed

**Subject recruitment**

Recruitment process: Through the 2 routes previously identified

- Payment of participants.

Subjects will be given reasonable travel and parking expenses. Subjects will also be provided with lunch or a voucher to cover their lunch if attending the centre fasting.

- Details of procedures, tests, screening carried out to assess trial suitability.

Screening will be via interview and symptom review with a study doctor

- Provision of patient information sheet (see appendix 1).
- Gaining patient consent

Consent will be obtained by a trained member of the research team. This will be taken after a full history has been taken by a study doctor to investigate the potential risk to the subject and suitability for the study. As the study involves a number of validated questionnaires which are in English, it is important that English is the subject’s first language as interpretation may be effected if English is a second language.

- Detail of enrolment procedure.

Subjects having contacted the centre following initial information being sent to them as previously described, they will have the nature of the study explained to them prior to having information and nature of the study explained to them. Then the subjects will be invited to attend for consent and screening visit.

**Randomisation**

The randomisation will be performed by Campden BRI, UK. A computer generated randomisation list will be used to provide balanced blocks of patient numbers for each of the two treatment groups. A one to one treatment allocation will be used. The block size will not be revealed.

**Blinding and other measures taken to avoid bias**

The study will be double blind, with the active being snack bar containing 100mg aspartame and the placebo being an identical bar containing no aspartame. Blinding will be done at manufacture and the code will be placed in a sealed envelope only to be opened in emergency.

**Subject compliance**

Subjects will need to eat at least 75% of the bar.

Subjects will be reviewed by the study team 48 hours after their withdrawl to monitor any adverse events.

**Withdrawal of Subjects**

**If a subject is withdrawn, follow up by telephone with the study team 48 hours, to review any adverse events. Where possible they will be replaced in the study.**

**Treatment of subjects**

The treatment will be with 2 snack bars given individually on 2 separate days 1 week apart, 1 bar containing 100mg of aspartame the other being aspartame free. Other ingredients include spices, crisped rice and dried fruit.

**General information**

Snack bar containing aspartame (or aspartame free)

**Use of treatment within the trial**

The snack bar is to be eaten by fasting subjects, subjects will be asked to eat 2 bars given in a double blinded and randomised order, 1 containing aspartame and 1 is aspartame free. These bars will be given to the subjects 1 week apart

Subjects will be eating the bars in the centre and study staff will check that at least 75% of the bar is eaten.

Each bar contains either no or 100mg aspartame

A dispensing / compliance log will be kept with the case report form.

Bars will be made in accordance with Good Manufacturing Practice*.* Shelf life will be adequate for the duration of the trial

The bar will not necessarily be available for commercial use following the trial, a registered dietitian will be available to participants to discuss the role of aspartame and artificial sweeteners in their diet.

It is important that the participants are not taking regular medication

No changes in medications are permitted during the trial except general over the counter treatments, e.g. painkillers

**Efficacy Assessments**

**Efficacy will be measured by insulin, glucose, gut hormones and inflammatory markers.**

**All samples will be stored and batched for analysis at the end of the study.**

**As detailed above** Imperial College, London will be subcontracted to measure aspartame and its breakdown products in blood and urine by the use of metabolite analysis using NMR and mass spectrometry. Samples will be sent to them in an anonymous manner to preserve confidentiality.

**Safety Assessments**

This is a safety study, assessing the effect of aspartame will be by questionnaires and symptom diaries along with a review of the biochemical results.

These will be analysed at the end of the study, as these effects are likely to be small.

No serious adverse events are expected in the trial.

Detail the procedures that will be followed in the event of adverse events in the trial. *Adverse events will be reported in accordance with HEYHT R & D department adverse event reporting procedures. Serious adverse events will be notified to HEYHT R & D dept. within 24hrs of investigators becoming aware of the event using the SAE/SUSAR initial and follow-up report forms provided by R & D. All adverse events (serious and non-serious) will be recorded in patients data collection forms (CRFs) using R & D’s adverse event report form. All adverse events will be recorded in patients medical records.*

All subjects following an adverse event will be followed by the research team 4 weeks following the reported event.

**Data collection**

Data will be collated in patient notes and a case report form in line with trust guidelines and good clinical practice.

This study consists of 3 visits, blood samples and questionnaires will be used to collect data at each visit.

Data will be collected by the study team, this will include a research nurse, dietitian and medical registrar. Data will be anonymised, with only be identified by a study number and the study identification.

Provide a detailed list of all data (outcome variables, explanatory variables etc) to be collected, with each description including:

**Sample Size**

The ability to estimate an appropriate sample size for the pilot is not possible as there are no comparable studies for guidance. This pilot will allow the main study to be powered appropriately on a specific factor. However, Power and sample size for pilot studies has been reviewed by Birkett and Day (Birkett MA, Day SJ. Internal pilot studies for estimating sample size. Statistics in Medicine 1994; 13:2455-2263). They concluded that a minimum of 20 degrees-of-freedom was required to estimate effect size and variability. Hence, we intend to recruit 50 patients per group (75-105 maximum) allowing for drop-outs and covariate adjustment.

.

**Statistical Analysis**

Data will be paired, tested for normality, if normally distributed will be analysed by paired t-test with 2 tails and non-parametric data will be analysed using Wilcoxon-signed rank testing. ANOVA will be used to account for any differences in the population e.g. smoking.

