**Study Design**

This is a double-blinded, placebo-controlled trial involving 50 self reported responders to aspartame (report that they have side effects when eating/ drinking products containing aspartame). Each participant will be given a single exposure to a bar containing aspartame as well as a matched placebo bar containing no aspartame. The dose of aspartame in the bars is 100mg, this is well below the Reference Daily Intake maximum recommended by EFSA of 40mg/kg body weight. In addition 25 participants with self-reported aspartame sensitivity and 25 matched control participants will be recruited to look at nocebo effect where they were given two lots of placebo (second part). The nocebo effect refers to the negative consequences of an inert treatment. The intention is to analyse the second part of the study only if any discriminating effect was observed between the two arms in the first part of the study.

*Plan for trial*

*Visit 1:*

Consent

Height, weight and waist measurements

Baseline bloods: full blood count and biochemical profile for safety

Baseline questionnaires of health and symptoms

- Beck depression inventory (BDI)
- Hospital Anxiety and Depression Scale (HADS)
- Trait anxiety perceived stress scale (STAI)
- Life events in last 5 years and 12 months (SRRS)
- Toronto Alexithymia scale
- Whiteley Index of Hypochondriasis

*Visit 2:*

Attend fasting

Fasting bloods: insulin, glucose, GLP1, GIP, biochemical profile and glucose

Give test or placebo challenge snack bar

Use of Visual Analogue Scales to assess effects of the aspartame/ placebo every 15 minutes for 2 hours, then at 3 hours and at 4 hours

Repeat bloods 4 hours following the consumption of the bar: insulin, glucose, GLP1, GIP, biochemical profile and glucose.

After lunch and recording of any adverse events or symptoms, subjects go home.

Telephone call 48 hours after visit to remind about questionnaires and monitor any side effects

One week between visits.

*Visit 3:*

Attend fasting

Fasting bloods: insulin, glucose, GLP1, GIP, biochemical profile and glucose

Give test or placebo challenge snack bar

Use of Visual Analogue Scales to assess effects of the aspartame/ placebo every 15 minutes for 2 hours then at 3 hours and at 4 hours

Repeat bloods 4 hours following the consumption of the bar: insulin, glucose, GLP1, GIP, biochemical profile and glucose.

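### Insulin, glucose, GLP1 and GIP have a fasting baseline at both test visits, but the stated paired test gives it no role; adjusting for it costs almost nothing and may add useful power.

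*Protocol*

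**What the plan says.** The visit plan in Study Design lists, at both Visit 2 and Visit 3, "Fasting bloods: insulin, glucose, GLP1, GIP, biochemical profile and glucose" and then "Repeat bloods 4 hours following the consumption of the bar: insulin, glucose, GLP1, GIP, biochemical profile and glucose". The schedule table agrees. Under Use of treatment within the trial, "subjects will be asked to eat 2 bars given in a double blinded and randomised order, 1 containing aspartame and 1 is aspartame free". Efficacy Assessments gives these markers their role: "Efficacy will be measured by insulin, glucose, gut hormones and inflammatory markers". Primary Endpoints also names acute effects on biochemistry, and the power needed for a larger study.

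The Statistical Analysis section has two sentences. The first reads "Data will be paired, tested for normality, if normally distributed will be analysed by paired t-test with 2 tails" and continues that "non-parametric data will be analysed using Wilcoxon-signed rank testing". The second reads "ANOVA will be used to account for any differences in the population e.g. smoking". Sample Size adds "we intend to recruit 50 patients per group (75-105 maximum) allowing for drop-outs and covariate adjustment", without naming a covariate.

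**The concern.** A paired t-test or signed-rank test uses one pair per person, and here there are four values per marker. The section does not say which two values, or which two derived quantities, form the pair. The only other model, ANOVA, is assigned to differences between people such as smoking. The fasting value taken just before each bar therefore has no stated use.

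In a crossover, stable differences between people cancel in the within-person contrast, but day-to-day shifts in a person's starting level do not. A baseline at each visit is the measurement that can remove them. If it is left out, that variation stays in the error term of the aspartame-placebo comparison. It also stays in the SD that the pilot passes to the main trial, where it could make the required sample size larger than an adjusted analysis would need.

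**Working it through.** **Inputs from the protocol.** Two test visits × two samples (fasting, 4 hours) = 4 values per marker per person, for insulin, glucose, GLP1 and GIP. Group size 50, so a paired test has 50 − 1 = 49 degrees of freedom. Two-sided test.

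**Assumptions, because the protocol gives no figure.** Significance level 5%. True aspartame-minus-placebo difference of 0.4 SD of the 4-hour paired differences. Correlation r between the fasting and the 4-hour aspartame-minus-placebo differences, from 0 to 0.6.

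The protocol has no power figure to reproduce. The 50 per group rests on a minimum of 20 degrees of freedom, and nothing below depends on that.

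**Notation.** For each person, D4 is the 4-hour value after aspartame minus the 4-hour value after placebo, and D0 is the same difference in the fasting values. Scale so that SD(D4) = 1.

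**Three bar-versus-bar analyses** (power from the noncentral t):

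1. Unadjusted, mean of D4. Error SD 1; noncentrality 0.4 × √50 = 2.83; df 49. Power 79%.
2. Paired test of the two within-visit changes, mean of D4 − D0. With equal variances the error SD is √(2 − 2r); df 49.
3. D4 regressed on D0, with the intercept as the bar effect. Error SD √(1 − r²); noncentrality 2.83 / √(1 − r²); df 48.

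| r | Unadjusted | Change score | Adjusted | Equivalent n, 50/(1 − r²) |
|---|---|---|---|---|
| 0 | 79% | 50% | 79% | 50 |
| 0.3 | 79% | 65% | 83% | 55 |
| 0.5 | 79% | 79% | 89% | 67 |
| 0.6 | 79% | 87% | 93% | 78 |

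The ratio of change-score to adjusted error variance is 2(1 − r)/(1 − r²) = 2/(1 + r), which is at least 1 for every r. More generally, regression picks the multiple of D0 that minimises the error variance, whereas the unadjusted analysis fixes that multiple at 0 and the change score fixes it at 1.

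**Small correction.** The adjusted column treats the mean fasting difference as zero. Averaging over its chance variation gives 78.3%, 82.0%, 88.6% and 92.9%, so adjustment loses just under one point at r = 0.

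**Check by simulation** (10,000 trials per setting, n = 50, true effect 0.3 SD). Variance components for person/visit/residual were 0.5/0.1/0.4 and 0.5/0.35/0.15, so Var(D4) = 2 × (visit + residual) = 1 in both, and r = 0.1/0.5 = 0.2 or 0.35/0.5 = 0.7.

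| r | Unadjusted | Change score | Adjusted |
|---|---|---|---|
| 0.2 | 55% | 38% | 56% |
| 0.7 | 55% | 76% | 82% |

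With no true effect, all three analyses kept false positives between 4.7% and 5.3%, including when a fasting-to-4-hour change of up to 1 SD was shared by both bars. All three are valid, and they differ only in precision.

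**The case against.** **The unadjusted comparison is sound, and the gain is uncertain.** Both parts stand. Type I error is held, the gain is nil at r = 0 and about 4 points at r = 0.3, and nothing in the protocol tells us r. This is also a pilot with no powered hypothesis.

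**The detail may be in a statistical analysis plan that is not shown, and Sample Size already allows for covariate adjustment.** This stands in part. Leaving the pair undefined would not be a finding by itself. But the protocol names a test, and that test as written has no place for a baseline. The covariate remark does not mention the fasting values, and the ANOVA sentence points to differences between people.

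**A reader might infer something stronger:** that the test must either discard the fasting values or credit to aspartame any change caused by eating a bar or by four hours passing. The documents do not support this. A paired test of the two within-visit changes also fits the wording; it uses all four values and cancels a shared change. The damaging version needs a fasting-versus-4-hour test within the aspartame visit alone. Such a test would indeed misfire: with no aspartame effect, a shared change of 0.2, 0.3 or 0.5 SD of the within-visit change would be significant in 28%, 55% or 93% of trials. But nothing says this is planned, and in a randomised placebo crossover the natural pair is aspartame against placebo. For the same reason no separate time term is needed.

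**Limits of scope.** The point does not cover every blood test: the full blood count is taken only at Visit 1, and the inflammatory markers named under Efficacy Assessments are in no blood list. Nor does adjustment make the SD estimate itself more precise (48 against 49 degrees of freedom). It can make the SD smaller, and the unadjusted SD remains the right input for an unadjusted main trial.

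**Conclusion.** The point holds as a nearly free improvement, not as an invalid analysis. For insulin, glucose, GLP1 and GIP, the stated paired test leaves out baselines that are collected at both visits. With 50 people and an assumed 0.4 SD difference, adjustment moves power from 79% to between 79% and 93% as the assumed correlation runs from 0 to 0.6; at a correlation of 0.5 it is worth about 17 extra people (67 against 50). The size depends wholly on a correlation that the protocol does not give. The evidence does not support a claim of inflated false positives under any bar-versus-bar reading.

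**What to change.** In Statistical Analysis, define the biochemical contrast for these four markers as the within-person 4-hour aspartame-minus-placebo difference, adjusted by regression for the fasting aspartame-minus-placebo difference, with the intercept (at zero fasting difference) as the bar effect. For markers that are clearly non-normal, transform before the regression or use a rank-based version, so that the existing provision for such data is kept. State that tests of fasting against 4 hours within a visit are descriptive, since they do not compare the randomised bars. Report both the unadjusted SD of the paired differences and the residual SD, so that the main trial can be sized for whichever analysis it adopts.

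The change is to wording only. It costs one degree of freedom of 49, with a power loss of under one point if the baselines turn out to be uninformative, and it needs no new samples or visits.

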**Protocol S1**

**Full Title: Determination of the symptoms of aspartame in subjects who have reported symptoms in the past compared to controls: a pilot double blind placebo crossover study**

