**FSA – Food Standards Agency**

**Background information**

Prior research investigating the potential health effects of aspartame have been criticised by lobby groups as the work to date is not robust due to poor methodology or confounded as aspartame was not the main focus of the study. To prepare for a definitive study it is thought that a pilot study is necessary to prove the methodology, the preparation to be used and the acceptability of the study to the scientific community, food regulatory and other stakeholders. This will allow an extensive and comprehensive study to be powered appropriately.

This double blind pilot study aims to utilise a defined product, assess the efficacy of the necessary psychometric and biochemical methodologies to determine whether the perceived effects of aspartame can be detected in sufferers (of aspartame effects) compared to non suffers. This will allow the preparation of a full trial to be accurate in terms of endpoints studied, numbers of participants etc.

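### The stated paired tests estimate only the within-person aspartame effect; nothing in the Statistical Analysis section commits to the sufferer-versus-control comparison that the protocol sets as its question

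*Protocol*

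**What the plan says.** **The question.** The protocol's title reads "Determination of the symptoms of aspartame in subjects who have reported symptoms in the past compared to controls" and calls the study a crossover. Background information states the aim as "to determine whether the perceived effects of aspartame can be detected in sufferers (of aspartame effects) compared to non suffers". Subject selection says "This study has 2 groups of subjects, those who report having symptoms when consuming aspartame and those who consume aspartame with no ill effects" and plans 50 in each group. Primary Endpoints also lists a question that needs no control group: "To study the acute effects of aspartame on psychological symptoms, biochemistry and metabonomics". The same aim appears under Aims and Objectives.

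**The analysis.** Statistical Analysis commits to specific tests: "Data will be paired, tested for normality, if normally distributed will be analysed by paired t-test with 2 tails", or the Wilcoxon signed-rank test for non-parametric data. It then adds "ANOVA will be used to account for any differences in the population e.g. smoking". It names no test between sufferers and controls, no group-by-bar term and no period term.

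**The design.** Use of treatment within the trial says "subjects will be asked to eat 2 bars given in a double blinded and randomised order", one week apart, and Randomisation gives 1:1 allocation in balanced blocks. Study Design differs on who eats what. There, 50 self-reported responders receive both bars, and a second part has 25 reporters and 25 matched controls who receive placebo twice.

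**The concern.** In a crossover with two kinds of participant, asking whether aspartame acts differently in sufferers than in controls means comparing within-person differences between groups. That is the bar-by-group interaction. A paired t-test or signed-rank test yields one aspartame-minus-placebo contrast, either in a single group or averaged over everyone. Neither version estimates sufferers minus controls.

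Two things are at stake. First, with no between-group test named, a group conclusion may end up resting on a significant result in one group and a non-significant result in the other, which is not a valid comparison. Second, determining the power for a large study is a stated purpose of this pilot. An SD and effect taken from the paired contrast would be carried into a main study whose group comparison needs many more people.

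A smaller point concerns the two visits. Bar order is randomised, but the named test has no period term, so any systematic difference between visits enters the error SD.

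**Working it through.** **Inputs.** From the protocol: 50 per group, two bars per person, randomised order, 1:1 balanced blocks, two-tailed paired test. Assumed, because the protocol gives no values: alpha 0.05, 80% power, and period effects of 0.25 to 1.0. All effects are in SDs of the within-person difference.

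**The plan's own figure.** Sample Size justifies 50 per group by a minimum of 20 degrees of freedom and gives no effect size, SD, alpha or power, so there is no power figure to reproduce. A paired test in 50 people has 50 − 1 = 49 df. A comparison of differences between 50 and 50 has 100 − 2 = 98 df. Both exceed 20, so the rule does not show which contrast the study was sized for.

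**Detectable effect at 80% power.**
- Within one group: (1.960 + 0.842)/√50 = 0.396; exact noncentral t gives 0.404.
- Between groups: (1.960 + 0.842) × √(2/50) = 0.560; exact noncentral t gives 0.566.
- At a true 0.4 SD, power is 79% for the paired test and 51% for the between-group test.

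**Consequence for the main study, at 0.4 SD (normal approximation).**
- Paired contrast: 2.802²/0.4² ≈ 49 people.
- Group contrast: 2 × 2.802²/0.4² ≈ 98 per group, 196 in all, about four times as many.

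**Risk if two paired tests are set side by side.** If both groups have the same true effect and each test has power p, the two verdicts differ with probability 2p(1 − p).
- p = 0.8: 2 × 0.8 × 0.2 = 32%.
- p = 0.5: 2 × 0.5 × 0.5 = 50%.
- Half of these disagreements would read as an effect in sufferers only.
- In 20,000 simulated trials with equal effects of 0.2 to 0.4 SD, the verdicts differed in 33% to 50%, and 16% to 25% were significant in sufferers only. A direct comparison of the differences was falsely significant in about 5%.

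**Period.** With effect τ and a difference π between the two visits, a person's aspartame-minus-placebo difference is centred on τ + π in one order and τ − π in the other. With a 25/25 split the mean is τ, so there is no bias, but the SD is estimated as about √(1 + π²).

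| Assumed π | SD overstated by | Type I error | Power at 0.4 SD |
| --- | --- | --- | --- |
| 0 | 0% | 5% | 79% |
| 0.3 | 4% | 4.1% | 77% |
| 0.5 | 12% | 2.8% | 72% |
| 1.0 | 41% | 0.6% | 49% |

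With period in the model, simulated power stayed at 79% for period effects of 0.25, 0.5 and 1.0.

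If dropout left the orders at 30/20, the paired estimate would be biased by π × (30 − 20)/50 = 0.2π. That is 0.05, 0.10 and 0.20 SD for π = 0.25, 0.5 and 1.0, with type I error of 5.6%, 7.0% and 8.3%.

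**Can the group contrast be estimated?** Study Design has 50 responders, then 25 reporters and 25 controls: 50 + 25 + 25 = 100. Subject selection has 50 + 50 = 100. The totals agree but the compositions do not. On the Study Design account no control eats an aspartame bar, so bar-by-group cannot be estimated. On the account in Subject selection and Use of treatment within the trial it can.

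**The case against.** The strongest defence is that the paired test fits one of the protocol's questions. Primary Endpoints and Aims and Objectives both list the acute effect of aspartame, which is a within-person contrast, and on the Study Design account a paired test in 50 responders is a natural choice. This stands. A reader might infer that the analysis answers nothing the trial asks, and the documents do not support that.

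The ANOVA sentence can also be defended. Smoking is given only as an example, and a repeated-measures ANOVA could carry group as a between-person factor. This stands in part: the wording does not exclude a group term, but it does not commit to one either. The additive effect of a fixed trait such as smoking cancels from a within-person difference; only its modification of the bar effect would remain.

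The opening words about pairing could be read as matched sufferer-control pairs. Matching is stated only for the 25 + 25 second part, so this does not supply the missing comparison.

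A reader might infer that a group conclusion is planned from two separate p-values. The protocol says no such thing. The 32% to 50% disagreement describes a risk left open, not an intended rule.

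On period, such a term is commonly left to the statistical analysis plan, which is not at hand. A reader might also infer that omitting it stops the question being answered, or that 50 people then carry the information of fewer. Neither follows. With balanced order the estimate is unbiased and its true sampling variability is unchanged; only the estimated SD and standard error are too large. The sizes of period effect used here are assumptions with no basis in the protocol.

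**Conclusion.** The concern holds as a mismatch between a stated method and a stated question. The title and Background information ask about sufferers against non-sufferers, and Subject selection recruits two groups of 50. Statistical Analysis nevertheless commits to tests that estimate only the within-person effect. Because specific tests are named, this is more than detail left to a later plan.

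Under the assumed two-sided alpha of 0.05 and 50 per group, the detectable effect is 0.57 SD for the group contrast against 0.40 SD for the paired one. The main study must be sized on whichever contrast it will test. The between-group figure applies only if controls receive both bars, which the protocol states inconsistently.

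The missing period term is secondary. With balanced order it makes the test conservative and passes an overstated SD to the main study, by 4%, 12% or 41% for assumed period effects of 0.3, 0.5 or 1.0 SD. It biases the result only if the two orders become unequal.

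**What to change.** 1. Reconcile Study Design with Subject selection and Use of treatment within the trial, so that the protocol states once which participants receive both bars and which receive placebo twice.
2. If controls receive both bars, add to Statistical Analysis a direct between-group comparison of the within-person differences. One suitable form is a mixed model with bar, period, group and bar-by-group as fixed effects and participant as a random effect. Report bar-by-group with a 95% confidence interval, alongside the bar effect within reporters.
3. If controls do not receive both bars, restrict the question in the title and Background information to the aspartame effect within reporters.
4. In either case, include period in the within-person analysis, report the period-adjusted SD of the differences, and state which contrast the main study will be sized on.

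If the reconciled design gives controls both bars, the analysis change costs only wording and one or two degrees of freedom, with no new data. If it does not, the cost is a narrower stated question.
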